## Abstract

In every surgical subspecialty surgical site infection (SSI) or implant infections, although occur seldom, pose a threat to patients’ health. Risk factors of such states is diabetes mellitus (DM), considered one of the most widespread health-related problems of the 21st century. Orthopedists perform big joint replacements that usually concern older adults and therefore often deal with patients suffering from comorbidities. DM is frequently one of them and can furthermore often remain underdiagnosed. The other risk for complication is a rapid beginning of the rehabilitation which starts on the day following the surgery. To eliminate the debilitating impact of DM and hypoglycemia on surgical patients, we aim to investigate the relationship between the glycemia values and the postoperative outcomes in certain periods of time in patients undergoing orthopedic surgeries. Participants meeting inclusion criteria will have inserted a glycemia measuring device (Dexcom G5, Inc., San Diego, CA) in the periods of time. First time it will take place 14 days prior to the surgery and right after the surgery for the second time for the period of another 14 days. All patients will undergo standard total knee arthroplasty or total hip arthroplasty procedures. Patients will be assessed preoperatively and 14 days, 1, 3, 6, 12, and 24 months postoperatively. The assessment of the joint condition will consist of: patient-reported outcomes (The Knee injury and Osteoarthritis Outcome Score, Harris Hip Score, the Western Ontario and McMaster Universities Osteoarthritis Index [WOMAC]); assessment of potential SSI and cardiovascular complications (the Finnish Diabetes Risk Score [FINDRISC], the Systematic Coronary Risk Evaluation [SCORE]) and the clinical examination. To investigate the influence of orthopedic surgery (anesthesia) on glycemia and the significance and safety of early patients mobilization after the big joints surgeries. To investigate changes of glycemia in patients with normal glycemia metabolism, potentially protecting them from hypoglycemia during hospital stay and increasing their awareness of potential development of DM in the future. Additionally, this study will correlate perioperative glycemic levels with risk of cardiovascular events in one year follow-up, and its influence on SSI and implant complications.

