Basic analysis will include descriptive statistics of demographic characteristics to assess both groups homogeneity. Such analysis will be done several times during testing to detect any confounders that could impact the results. Continuous variables will be summarized with number of cases, means, standard deviations, medians, ranges, and first and third quartile (Q1 and Q3). All comparisons will be performed between continuous variables in paired groups, therefore either a 2-sided Student *t* test for paired groups or Wilcoxon Signed Rank test will be used. Distribution normality will be examined using the Shapiro–Wilk test. An overall alpha-level of 0.05 will be used as a cut-point for statistical significance and all statistical tests will be 2-sided. Significance level will be set at *P* value below .05. Outliers will be initially identified using interquartile range (IQR) as observations with values above Q3-1.5IQR or below Q1-1.5IQR and will be examined individually. All data will be presented with extreme and outlier observations or committed with appropriate annotation.

All statistical analyses will be conducted using SAS 9.4 for Windows (SAS Institute Inc., NC).

The study protocol was published before the start of the study on clinicaltrials.gov. The results of the study will be published in (inter-)national scientific journals and guidelines. The data that support the findings of this study will be available from the corresponding author - OA, upon reasonable request.

Data reported in the presenting study will be prospective observational data. The treatment will be reliable to the patients’ condition. And the procedure of implementing the glucose measuring device will be the same throughout the whole cohort. This has to be kept in mind for the interpretation of the results.

The inclusion and exclusion criteria presize how the authors deal with the risk of bias such as severity of illness or presence of comorbidities on intervention group assignment.

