## 4. Outcomes measure

### 4.1. Primary outcomes

Changes of glycemia levels during 4-week perioperative period: mean glucose level during pre- and postoperative period, 24-hour glucose level amplitude, time of both higher and lower glucose level than average for the day in total, number of periods of both higher and lower than average glycemia levels for the day and its’ duration, number of days with higher mean glucose level than the mean for the corresponding pre- and postoperative period;Any cardiovascular events during follow-up (heart stroke, brain stroke, coronary arteries disease, transient ischemic attack;Any surgical site and/or implant complications during follow-up.

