### 4.2. Secondary outcomes

Objective functional outcome in Knee Injury and Osteoarthritis Outcome Score (KOOS) or HHS scale and WOMAC;Correlation of FINDRISC scale results with cardiovascular events and/or surgical site or implant complications.

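### The paired-tests-only rule cannot test the two primary event outcomes and contradicts the unpaired comparison behind the sample size

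*Protocol article*

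**What the plan says.** Section 3 (Ethics, data management, and statistical analysis) sets one rule for inference: "All comparisons will be performed between continuous variables in paired groups". It draws the choice of test from that rule ("therefore either a 2-sided Student" t test for paired data, or the Wilcoxon signed-rank test). No other inferential test is named, and summary statistics are described only for continuous variables.

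Section 4.1 lists three primary outcomes:
- "Changes of glycemia levels during 4-week perioperative period", a set of sensor measures before and after surgery;
- "Any cardiovascular events during follow-up";
- "Any surgical site and/or implant complications during follow-up".

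Section 4.2 adds as a secondary outcome "Correlation of FINDRISC scale results with cardiovascular events and/or surgical site or implant complications". The Abstract says that "this study will correlate perioperative glycemic levels with risk of cardiovascular events in one year follow-up", and the Discussion repeats this together with the influence on infection and implant complications.

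The power analysis, also in Section 3, takes its effect size from the difference in means between patients who do and do not have a complication. It uses 0.6 on the Cohen scale, significance level 0.05, a value of 0.8 labelled beta, and 1:1 allocation. The result is 90 patients, raised to 100 for 10% dropout.

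**The concern.** A paired test needs two measurements of the same quantity on the same patient. An event recorded during follow-up supplies one yes/no value per patient and has no value before surgery to set against it. Patients with an event and patients without one are different people, so comparing their glycaemia is an unpaired comparison. The stated rule covers neither case.

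This is more than a detail left to a fuller document. The sentence is universal and gives its reason, so a later analysis plan could not add an unpaired comparison without contradicting it. Followed as written, the study would test pre/post changes in glycaemia and function only. Any method relating glycaemia to complications, the comparison on which the study was sized, would be chosen after the data are seen.

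**Working it through.** **Which outcomes the two named tests can handle**

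| Outcome | Type | Preoperative counterpart | Paired t or signed-rank test |
|---|---|---|---|
| Glycaemia measures (primary) | continuous | yes | fits |
| Cardiovascular events (primary) | binary | no | cannot be applied |
| Surgical site or implant complications (primary) | binary | no | cannot be applied |
| Functional scores (secondary) | continuous | yes | fits for pre/post change |
| FINDRISC and events (secondary) | score against binary event | no | does not fit |

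**Reproducing the sample size**

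Inputs from Section 3: d = 0.6, two-sided α = 0.05, 1:1 allocation. The 0.8 labelled beta is read as power.

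- Two independent means, normal approximation: n per group = 2(1.960 + 0.842)² / 0.6² = 2 × 7.85 / 0.36 = 43.6, so 44 per group and 88 in total.
- The same design with the noncentral t distribution: 44.6, so 45 per group and **90 in total**, exactly the stated figure. Dropout: 90 / (1 − 0.10) = 100, also as stated.
- One-sided two-sample t test: 35.04, so 36 per group and 72 in total. No match.
- Paired t test at d_z = 0.6, where d_z is the mean difference divided by the SD of the differences: 23.8, so **24 patients**. No match. With 90 pairs, power at d_z = 0.6 would exceed 99.9%, and d_z of about 0.30 would be detectable with 80% power.

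The stated size is therefore that of an unpaired comparison, which the analysis rule leaves no room for.

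**How many events to expect in 90 patients**

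- Section 6 (Discussion) cites a major cardiac complication rate of 0.2% to 0.8%. Expected events: 90 × 0.002 = 0.18 to 90 × 0.008 = 0.72. Chance of none: 0.998⁹⁰ = 84% to 0.992⁹⁰ = 49%. The protocol's cardiovascular outcome is broader than this, so these figures mark the low end.
- The article gives no usable complication risk. Assuming 2% to 10%: 90 × 0.02 = 1.8 to 90 × 0.10 = 9, or about 2 to 9 events.

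**Power of an unpaired comparison at d = 0.6 with these numbers**

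Noncentrality = d × √(n₁n₂ / (n₁ + n₂)), with 88 degrees of freedom, two-sided 0.05.

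| Events / non-events | Noncentrality | Power |
|---|---|---|
| 45 / 45 | 0.6 × √22.5 = 2.85 | 80% |
| 18 / 72 | 0.6 × √14.4 = 2.28 | 61% |
| 9 / 81 | 0.6 × √8.1 = 1.71 | 39% |
| 5 / 85 | 0.6 × √4.72 = 1.30 | 25% |
| 2 / 88 | 0.6 × √1.96 = 0.84 | 13% |

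The planned 80% holds only if half of the patients have a complication.

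**What incidence alone can show**

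With no event in 90, the exact two-sided 95% interval runs from 0 to 1 − 0.025^(1/90) = 4.0%.

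**The case against.** The strongest reply is that the rule governs comparisons, while the FINDRISC outcome and the glycaemia–event link are described as correlations. A condensed article may leave the method for a correlation to the full protocol. That stands. A reader might infer that the plan forbids these analyses, but the text does not go so far: they are announced, and the only tests named do not fit them.

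A second reply is that events in a single cohort can be reported as incidence with no test. That also stands, but it leaves the comparison behind the sample size without a method.

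Third, the effect of surgery on glycaemia is itself a stated aim. The Discussion stresses that each postoperative measurement has a preoperative partner, and paired tests are right for that. The fault is that a rule suited to one part of the study was written as covering all of it.

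Three stronger readings should not be drawn. The check of "descriptive statistics of demographic characteristics to assess both groups homogeneity" does not prove that the design was misunderstood, because the groups are undefined and could be knee and hip patients, or patients with and without complications. Nothing suggests that patients would be paired arbitrarily to make the tests run. Nor does the article say that postoperative sensor data will be the exposure for early infections, so a charge of reverse causation has no basis in the text.

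Finally, few events limit any association analysis, whichever test is named. That is true, and is a reason to state the limit in advance.

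**Conclusion.** The rule is wrong as written. It cannot test two of the three primary outcomes, and it contradicts the power analysis in the same section, where 90 matches two independent groups of 45 and not the 24 patients of a paired test with the same numerical effect. For pre/post glycaemia and pre/post scores the named tests are appropriate. The FINDRISC and glycaemia–event correlations lack a suitable named method but are not prohibited.

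The sample-size conclusion rests only on the article's own inputs, with the 0.8 read as power. The event counts and power figures rest on assumed complication risks of 2% to 10% and d = 0.6. The cardiac figures rest on a cited rate narrower than the trial's outcome. Across these ranges any event analysis can be exploratory only.

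**What to change.** 1. Limit the paired-test sentence to pre/post glycaemia and pre/post functional scores.
2. For each event outcome, report incidence with an exact (Clopper–Pearson) 95% confidence interval.
3. Relate each event outcome to one pre-specified exposure measured over the same window in every patient, namely preoperative mean sensor glucose, and separately to FINDRISC. Use Firth logistic regression and label it exploratory. If there are too few events to fit the model, report the incidence only, with the minimum number set in advance.
4. State the expected number of events and the power that follows: 0.18 to 0.72 events at the cited cardiac rate, and about 2 to 9 events with about 13% to 39% power at assumed complication risks of 2% to 10%.

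A single named model leaves no choice of method once the data are seen. A preoperative window avoids giving patients with and without events different exposure periods.

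The cost is a paragraph in the analysis plan, a little more analysis work, and a less favourable statement of what the event analyses can show. No new data are needed.

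### An overall alpha of 0.05 is stated, but a family of primary glycaemia measures is tested at P < .05 each with nothing to control the family-wise error

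*Protocol article*

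**What the plan says.** Section 3 of the protocol article (ethics, data management and statistical analysis) gives the error level twice. First: "An overall alpha-level of 0.05 will be used as a cut-point for statistical significance", in a sentence that adds that "all statistical tests will be 2-sided". Then: "Significance level will be set at *P* value below .05". It mentions no multiplicity adjustment, testing order or lead outcome. On the tests themselves it says: "All comparisons will be performed between continuous variables in paired groups", by paired Student t test or Wilcoxon signed rank test.

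Section 4.1 opens its primary outcomes with a group of glycaemia measures: "mean glucose level during pre- and postoperative period, 24-hour glucose level amplitude", then "time of both higher and lower glucose level than average for the day in total", then the number and duration of periods above and below the day's average, and the number of days whose mean exceeds the mean of the corresponding period. Two further primary outcomes follow: cardiovascular events, and surgical-site or implant complications.

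The sample size paragraph in section 3 assumes one comparison at .05, with an effect size of 0.6 between groups with and without complications.

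**The concern.** An overall alpha of 0.05 is normally read as a limit on the chance of any false-positive claim among the primary tests. A threshold of .05 applied to each test does not give that limit when several primary measures are tested. As written, a P value below .05 on any one glycaemia measure could be reported as a positive primary result, and the reader would take the error rate behind it to be 5%.

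This matters because the study has confirmatory features: designated primary outcomes, a power calculation and a significance threshold. Section 3 foresees use in guidelines, and the Discussion foresees a perioperative care algorithm.

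**Working it through.** **Reproducing the plan's own figure.** Inputs from section 3: effect size 0.6, alpha .05 (two-sided), 0.8 (called beta, but the figure reproduces only if it is read as power), 1:1 allocation. A two-sample t test with the noncentral t distribution needs 44.6, so 45 per group and 90 in total. Allowing for 10% dropout, 90 / 0.9 = 100. Both figures are reproduced, for a single comparison at an unadjusted .05.

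**Counting the family.** As worded, section 4.1 yields nine glycaemia measures:
- mean glucose (1) and 24-hour amplitude (2);
- time above (3) and below (4) the day's average;
- number of periods above (5) and below (6) it;
- duration of periods above (7) and below (8);
- number of days above the period mean (9).

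Several of these overlap by definition. Time above plus time below equals monitored time, apart from ties and sensor gaps, so with equal monitored time the two changes are mirror images and give the same two-sided result. High and low periods alternate, so their daily counts differ by at most one. If duration means duration per period, it is time divided by number of periods. That leaves mean, amplitude, time, number of periods and number of days, which is five measures, or six if duration is kept as one more.

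The two event outcomes are not counted. They are yes/no outcomes during follow-up, and section 3 states no test for them.

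**Error rate if no measure changes.** For k independent tests the chance of at least one P < .05 is 1 − 0.95^k:
- k = 5: 1 − 0.95^5 = 0.226
- k = 6: 1 − 0.95^6 = 0.265
- k = 9: 1 − 0.95^9 = 0.370

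The article gives no correlations, so a common correlation r between normal test statistics is assumed. With φ and Φ the standard normal density and distribution function, the rate is 1 − ∫ φ(u) [Φ((1.96 − √r·u)/√(1−r)) − Φ((−1.96 − √r·u)/√(1−r))]^k du:

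| Tests | r = 0 | r = 0.5 | r = 0.7 | r = 0.9 |
|---|---|---|---|---|
| 5 | 0.226 | 0.183 | 0.148 | 0.102 |
| 6 | 0.265 | 0.207 | 0.164 | 0.108 |
| 9 | 0.370 | 0.269 | 0.202 | 0.124 |

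For jointly normal two-sided tests the independent case is the largest (Šidák inequality), so 0.370 is an upper figure for nine tests.

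**Power after adjustment.** Bonferroni over nine gives 0.05/9 = 0.0056 per test; Holm is never less powerful.
- Paired basis, with 0.6 assumed to be the standardised paired difference: 90 pairs, noncentrality 0.6 × √90 = 5.69, 89 degrees of freedom. Power is 0.997.
- Two-group basis, as the study was sized: 45 per group, noncentrality 0.6 × √(45/2) = 2.85, 88 degrees of freedom. Power falls from 0.80 to 0.50. Restoring 80% would take 150 patients instead of 90.

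**The case against.** The strongest objection concerns the word *overall*. A cut-point is a per-test threshold, and the article soon repeats it as P below .05, so the word may mean no more than *throughout*. That reading is plausible. If it is right, no guarantee has been broken, but the sentence misleads and no family-wise control exists, so it still needs correcting.

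A second objection is that multiplicity is commonly left to an analysis plan, that a plan may exist unseen, and that this is a condensed article on an observational cohort. This stands as far as the absence of a procedure goes. It does not cover the wording, because the article itself calls the level overall, fixes P below .05 and ranks the whole family as primary.

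A third objection is that section 4.1 can be read as three primary outcomes, with glycaemia as one outcome in several components. That changes the label only: no rule combines the components into a single test.

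Two stronger readings are tempting but not supported. A reader might count eleven primary tests, adding the two event outcomes, and quote 1 − 0.95^11 = 43%. Section 3 describes only paired comparisons of continuous variables, which do not fit those outcomes, and the figure also ignores the overlap among the glycaemia measures. A reader might also infer that the sample size relates to none of the primary outcomes. Section 3 refers to groups with and without complications, and complications are a listed primary outcome. The mismatch between two-group sizing and paired testing is a separate matter.

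**Conclusion.** The concern holds for the glycaemia family. On the plain reading of section 3, the plan states an overall level of 5% that testing each measure at P < .05 does not deliver. For five or six distinct measures the chance of at least one false-positive result runs from about 10–11% (r = 0.9) to 23–26% (independent), that is, roughly two to five times the stated level. The figure of 37% is an upper limit that treats all nine measures as independent, which their definitions rule out.

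These rates assume that no measure truly changes, that each measure is tested once by a paired pre/post test, and that correlation is common to all pairs. The count of five or six depends on reading duration as duration per period. The conclusion does not depend on the exact figure, since every case in the table is at least about twice 5%.

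**What to change.** Before analysis, do one of the following:
- Name one primary glycaemia measure for the paired pre/post comparison, for example the within-patient change in mean sensor glucose, at two-sided 0.05, and make the others secondary. The choice of measure is the investigators'.
- Keep the family primary, list its non-redundant members, and apply Holm across them.

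In either case, report the event outcomes as estimates with confidence intervals. At minimum, delete *overall* and state that P < .05 is a per-test threshold with no family-wise control.

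No extra patients or data are needed to name one primary measure. The price is that fewer results can be called confirmatory. Adjusting across the family costs little power if 0.6 is a paired effect, but the article does not say that it is. On the two-group basis used for sizing, adjustment could cost as much as the fall from 0.80 to about 0.50 shown above, so naming one measure is the cheaper option.

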## 3. Ethics, data management, and statistical analysis

All procedures used for this study have been approved by the Institutional Bioethics Committee of the Medical University of Warsaw (number of approval: KB/104/2020). The study was registered in the ClinicalTrials.gov database (NCT04484480). All patients will be obliged to give written consent for their participation in the study. Collected data will be stored at the Department in a database created particularly for this study and secured appropriately. In the database each participant will have a special code to minimize the risk of identification of a particular patient. Only patients who attend all visits, fill in all questionnaires and do not interrupt the course of the study in any other way will be included in the analysis. The consequence of the absence on a control visit will be exclusion from the study.

Power analysis was performed to assess how many patients should be included in the study. Determining effect size was hindered by lack of literature comparing mean values and standard deviations (SD) between groups with and without complications. The effect size can be deemed “large,” described numerically as 0.8 by Cohen. However, we decided to be more conservative and used an effect size of 0.6, located between “medium” and “large” in Cohen scale. Standard *P* value of .05, beta value of 0.8, and allocation ratio of 1/1 were used, resulting in a total needed sample size of 90 patients. Taking into consideration that 10% of patients might drop off the follow-up predicted number of participants is 100.

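### The upper outlier fence is printed as Q3 − 1.5 IQR, which lies below the first quartile, and the sentence on handling flagged values is garbled

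*Protocol article*

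**What the plan says.** The rule is in section 3 of the protocol article (Ethics, data management, and statistical analysis). After the summary statistics, the paired tests and the Shapiro–Wilk check, the text says that an interquartile-range method gives a first identification of outliers, namely "observations with values above Q3-1.5IQR or below Q1-1.5IQR and will be examined individually". The same paragraph uses the symbols Q1 and Q3 for the first and third quartiles, so the notation is not in doubt.

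The next sentence deals with what happens to such values: "All data will be presented with extreme and outlier observations or committed with appropriate annotation".

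No other part of the article gives the rule in a different form or corrects the sign. The article does not say whether the rule is applied to single sensor readings or to per-patient summaries.

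**The concern.** The usual IQR rule sets the fences outside the box: 1.5 IQR above the third quartile and 1.5 IQR below the first. The lower fence is printed correctly. The upper one is subtracted instead of added, which puts it on the low side of the data, so the median and the whole central half count as outliers. Followed to the letter, the rule cannot separate unusual values from ordinary ones.

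The second sentence adds an uncertainty about consequences. It offers two alternatives joined by *or*: showing data with the outliers, or something rendered as *committed* with annotation. If that word stands for *omitted*, removal is an option and nothing on the page says when it applies. This matters because section 4.1 (Primary outcomes) lists measures to which extreme values contribute, among them the 24-hour glucose amplitude.

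**Working it through.** **Inputs.** The fences are as printed in section 3, with Q1 and Q3 the quartiles. The article states no proportion flagged, so there is no figure of its own to reproduce. The only stated quantity is the upper fence, and it does not match either standard IQR variant: the inner fence is Q3 + 1.5 IQR and the outer fence is Q3 + 3 IQR, and both add to Q3. The distribution shapes below are illustrative assumptions, since the document gives no glucose distribution. The finite-sample check uses the planned numbers: the power calculation is reported as "resulting in a total needed sample size of 90 patients", with 100 to be enrolled.

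**Step 1: where the printed fence lies, for any distribution.** IQR = Q3 − Q1, so Q3 = Q1 + IQR and

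Q3 − 1.5 IQR = Q1 + IQR − 1.5 IQR = Q1 − 0.5 IQR.

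This is never above Q1. About 75% of a continuous dataset lies above Q1, so at least about 75% is flagged whatever the shape. The only values that escape lie in a low band from Q1 − 1.5 IQR to Q1 − 0.5 IQR.

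**Step 2: normal data.** In SD units, Q1 = −0.6745, Q3 = +0.6745 and IQR = 1.349.

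- Printed upper fence: 0.6745 − 1.5 × 1.349 = −1.349. P(Z > −1.349) = 91.13%.
- Lower fence: −0.6745 − 1.5 × 1.349 = −2.698. P(Z < −2.698) = 0.35%.
- Flagged as printed: 91.13% + 0.35% = 91.5%. Not flagged: 8.5%.
- Standard upper fence: 0.6745 + 1.5 × 1.349 = +2.698. Flagged under the standard rule: 2 × 0.35% = 0.70%.

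**Step 3: planned sample sizes.** In 5,000 simulated normal samples each, the printed rule flags on average 91.5% at n = 90 and 91.4% at n = 100. The standard rule flags 1.1% and 1.0%. At n = 90 that is about 82 values (0.915 × 90) against about 1 (0.011 × 90).

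**Step 4: other shapes.**

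| Assumed distribution | Flagged as printed | Flagged with Q3 + 1.5 IQR |
|---|---|---|
| t, 5 df | 91.4% | 3.4% |
| Lognormal, sigma 0.25 | 94.2% | 1.8% |
| Lognormal, sigma 0.3 | 94.9% | 2.1% |
| Lognormal, sigma 0.5 | 97.7% | 3.8% |
| Exponential | 100% | 4.8% |
| Uniform | 100% | 0% |

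**Step 5: the handling sentence.** Two emendations of *committed* are possible. *Omitted* fits the contrast with data shown including outliers. *Commented* is close in spelling and fits the reference to annotation. Under the first, flagged values may be dropped. Under the second, all values are kept and explained. The text does not decide between them.

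**The case against.** The strongest reply is that this is a one-character slip in a condensed article. The method is named, the multiplier is the usual one and the lower fence is right. An analyst would probably program the standard rule, and anyone who coded the printed one would see the fault on the first run. That stands, and it limits the severity. It does not make the printed threshold correct, and no other sentence repairs it.

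A reader might infer more than the document supports:

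- **That the plan lets some 91% of the data be dropped.** It does not say so. The rule is a first screen, and flagged values are to be examined one by one. Removal rests on one reading of a garbled word and would be an annotated option, not an automatic step.
- **That leaving out extremes pulls the pre/post comparison toward no change.** The direction depends on which period holds the extremes. Removing high postoperative values would shrink an apparent rise, and removing high preoperative ones would enlarge it.
- **That examination would be done with the results in view.** The article does not say this.
- **That the rule strips glucose excursions from the sensor trace.** The unit is not stated. The rule follows text on summarising continuous variables, so it may apply to patient summaries, and an outlying patient mean is not the same thing as an excursion.

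It is also fair to say that detailed exclusion criteria are commonly left to an analysis plan that is not shown. Their absence is therefore not the point. The point is a threshold that is stated wrongly and a handling sentence that cannot be read with certainty.

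**Conclusion.** Wrong as written, and minor. The printed upper fence equals Q1 − 0.5 IQR and would flag at least about 75% of any continuous dataset for individual examination. That floor needs no distributional assumption. The 91.5% against 0.7% assumes normality, and the other shapes tried give 91% to 100% as printed against 0% to 5% with the standard rule. These figures describe the literal rule, not a likely outcome, because the minus sign is probably a slip for plus.

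The handling sentence is unclear. Only if *committed* means *omitted* does it allow flagged values to be left out without a stated criterion. In that case primary outcomes that depend on extremes, such as the 24-hour amplitude, could be affected, but neither the size nor the direction of the effect can be worked out from the document. Sample size and choice of tests are untouched.

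**What to change.** In section 3, define outliers as values above Q3 + 1.5 IQR or below Q1 − 1.5 IQR. Replace the sentence containing *committed* with a plain statement: flagged values stay in the primary analyses unless a device fault or data-entry error is documented, and results excluding flagged values are shown only as a sensitivity analysis.

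The cost is two sentences of text. Sample size, visits and data collection do not change.
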